### Phase 1 - qualitative study

Patients will be interviewed once face-to-face by a qualitative researcher. The interview format will be flexible to allow for logistics of the large area being covered by the study and interviews will take place either on an individual basis or with two or more patients together as appropriate. Interviews will be semi-structured to ensure that key themes are covered, whilst giving participants the opportunity to freely express their views.

The topic guide will explore participants’ views and experience of type 1 diabetes, and what information they were given about exercise at diagnosis (Table 2). All interviews will be recorded, and interviewing will continue until saturation is reached.

**Table 2 T2:** Topic guide for Phase 1 interviews

1) Moderator’s introduction	
2) About the group	
3) Activity and exercise behavior	What exercise do you do?
	What does the word ‘exercise’ mean to you? (focus on activity levels)
	Why should someone exercise?
	How active are you on a day to day basis/how do you feel about the amount of exercise you do?
	Do you think you do enough exercise to keep healthy?
	Is exercise important in the management of diabetes?
	What are the recommended guidelines?
	The DOH recommends 150 minutes exercise per week, what do you think of this?
	Do you think this is achievable?
	How do you relate to the recommended levels?
4) Barriers to exercise	What are the mains reasons for not meeting the guidelines?
	How do you try to overcome these barriers? How can you resolve them?
	If you have a fear of having a hypo, do you make any adjustments?
	If you had a magic wand what would be the one thing you could overcome in order to allow you to do more exercise?
	Has the diagnosis of diabetes changed your attitudes towards exercise?
	Does education and understanding have a role in the management of your diabetes and therefore your exercise levels?
5) Encouragement and facilitation of exercise	Can you think of any ways of improving your activity levels?
	How can small changes be incorporated into your lifestyle?
	Are there any major themes that would help encourage people to be more active?
	Would more advice or information help?
	If you had to choose one intervention that would help your activity levels - which would it be?
	Has anyone any successful experiences of exercising?
	We are thinking about doing a study - if you were to take part how would you like to be monitored / encouraged?
	One-to-one advice from a health and fitness advisor
	Attending an exercise group organized by the hospital or your GP
	Support - someone who keeps in touch to see how you are doing with your exercise program
	Goal setting/modification/action planning
	Heart rate monitoring
	Chat room with other people from the study to share ideas
	Uploading BMI/weight loss onto website - self monitoring
	If phone calls weren’t appropriate, what else could we do to motivate you?
6) Summary of session	Outlining main points of discussion and key issues raised
	Questions and thank everyone for their input

### Analysis

Data collection and analysis will be iterative to allow earlier data to shape later data collection. The transcribed data will be analyzed using constant comparative analysis to identify the emerging themes which comprise interviewees’ views regarding particular issues [35]. Themes from participants of different ages and gender will be compared and differences and similarities noted. Management of data for analysis will be assisted by the software package NVivo (QSR International, Victoria, Australia). Themes and a coding frame will be developed by reading and re-reading of the interview transcripts and through discussions between members of the multi-disciplinary research team.

Information from this phase will be used to refine the intervention developed for phase 2.

### Phase 2 - RCT

#### Pre-randomization visits

Patients will be initially screened on the telephone and potentially eligible individuals invited to attend a face-to-face assessment to confirm eligibility (visit 1). Here the study team will obtain informed consent, record their clinical history and conduct a physical examination. Participants will return in a fasting state to undertake baseline tests including the meal-stimulated C peptide measurement (visit 2, Table 3). Participants will return again to undertake Astrand-Rhyming and YMCA/ACSM cycle tests to assess fitness [36] (visit 3). Two cycle tests will be performed to ensure that we can get an accurate estimation of fitness. A study doctor will see all patients at visit 1.

**Table 3 T3:** Tests/action/questionnaires conducted at baseline, 6 and 12 months

Clinical examination	Cardiovascular/respiratory/gastrointestinal/nervous system/feet
	Blood pressure and heart rate
	Height, weight, waist circumference
	Body-fat content (bio-impedance)
Non-fasting blood collection	GAD, IA-2 and zinc transporter autoantibodies
	Full blood count/thyroid function
	Liver/renal function
	DNA (optional, only at visit 1)
Fasting blood collection	Cholesterol, LDL, HDL, triglycerides
	Serum/plasma storage
Inflammation markers	Adiponectin, leptin, IL-6, IL-10, CRP
Meal-stimulated C peptide	Participant attends fasting and drinks Fortisip 240 ml. Venous blood samples collected at time -10, 0, 15, 30, 60, 90, 120 minutes
Questionnaires	International physical activity questionnaire (IPAQ)
	Bandura exercise self-efficacy questionnaire
	Social support for physical activity scale
	Outcome expectations for exercise
	Deci and Ryan motivational questions TSRQ
	Health care climate questionnaire HCCQ
	Pittsburgh sleep quality index (PSQI)
	WHO quality of life-BREF
	Fear of hypoglycemia survey
	BRIEF illness perception
	Problem areas in diabetes (PAID)
	CES-D
	Toole and Glasgow dietary questionnaire
	EQ-5D
Activity monitor	Small electronic device worn during waking hours for seven days. Measures physical activity by continually monitoring and recording movements of the body
Fitness test	Estimation of VO2max by submaximal test
Nurse visit	Education on carbohydrate counting and insulin dose adjustment around exercise
	Review of exercise diaries
	Hypoglycemia management
	Motivational support
Focus group for feedback	Obtain feedback on the study

#### Randomization

Randomization will be done according to computer-generated allocation. Patients will be assigned, in a 1:1 ratio, to ‘usual care’ or ‘exercise intervention’. Allocations will remain concealed by the trial coordinator until the patients attends visit 4 when they will be randomized using on-line software. Randomization will be minimized by center, meal-stimulated 90-minute C peptide, and fitness. Due to the nature of the intervention, blinding of the study team to the randomization arm is not possible.

#### Post-randomization visits

In agreement with the local GPs and hospital doctors, the study team will undertake the ongoing diabetes management of all trial participants for the period of the trial. This is to ensure that similar guidelines for treatment intervention are maintained across all sites. Patients will be seen at baseline, 6 and 12 months by a doctor and any changes in treatment will be made according to strict guidelines, thus ensuring no bias between the two groups. All participants will have eight visits. Those patients randomized to the exercise arm will have a further five telephone consultations (see Table 4).

**Table 4 T4:** Visit overview

	**Pre-randomization**			**Randomization**	**Post-randomization**													
**Test/action**	**Visit 1**	**Visit 2**	**Visit 3**	**Visit 4 (wk 0)**	**Visit 5 (wk 2)**	**Visit 6 (wk 4)**	**Visit 7 (wk 8)**	**Visit 8 (wk 12)**	**Visit 9 (wk 16)**	**Visit 10 (wk 20)**	**Visit 11 (wk 24)**	**Visit 12 (wk 24)**	**Visit 13 (wk 30)**	**Visit 14 (wk 36)**	**Visit 15 (wk 42)**	**Visit 16 (wk 48)**	**Visit 17 (wk 48)**	**Visit 18 (wk 50)**
Clinical exam	x							x			x			x			x	
Questionnaires	x	x									x						x	
Activity monitor	x							x			x			x			x	
Non-fasting blood tests	x										x						x	
Fasting blood tests		x									x						x	
HbA1c	x							x			x			x			x	
Inflammatory markers		x									x						x	
Urine albumin/creatinine ratio		x									x						x	
Meal-stimulated C peptide		x									x						x	
Fitness test			x									x				x		
Nurse visit					x	X^a^	x	x	X^a^	x			X^a^	x	X^a^		X^a^	
Focus group feedback																		x

X: visit attended; wk: week. ^a^visit for exercise intervention arm only.

#### Usual care

Usual care will consist of standard dietary and exercise advice after randomization, and at the end of the study. There will also be reviews by a study doctor and nurse at baseline and at 6 and 12 months. At randomization, the dietitian will meet with the patients for 45 minutes to provide education on food intake as well as providing information on insulin and carbohydrate dose adjustment around exercise and hypoglycemia management. Any changes to medication will be made using a standardized staged protocol (see disease management).

#### Exercise intervention

Participants allocated this arm will receive dietary advice at baseline as for the usual care arm. Thereafter they will be seen by a physician at 6 and 12 months and will have nurse contact at 2, 4, 8, 12, 16, 20, 30, 36, and 42 weeks. Again, any changes to medication will be made using a standardized staged protocol (see Medical management).

Using goal-oriented motivational interviewing techniques, the aim of the physical activity intervention will be to encourage patients to safely increase and maintain their exercise level to at least 150 minutes per week, and aiming for 240 minutes per week of vigorous intensity exercise per week. This goal will be applied to all participants, regardless of their initial level of physical activity. The activity goal will be achieved gradually over 12 weeks in a step-wise fashion and then maintained for the remainder of the study (see Table 5). During the first week, participants will simply be encouraged to do something active on three to four days per week. This will be based outside the hospital setting and monitored as outlined below. On subsequent weeks, the activity level will be increased to 85, 100, 110, 115, 130 and finally 150 minutes per week. The intensity level will also gradually increase until the patient is performing at an intensity of 75% of their estimated maximum oxygen uptake. If participants do not achieve the physical activity goal within 12 weeks, they will be encouraged to achieve it as soon as possible thereafter. Participants will be encouraged and supported to achieve this goal, and will be instructed that they may accumulate activity throughout each day in bouts of at least 10 minutes. Participants who are active sporadically (for example, seasonally) will be encouraged to achieve the goal consistently throughout every month of the study.

**Table 5 T5:** Graded exercise protocol

**Week**	**Total minutes per week**	**Intensity (% VO2max)**	**Heart rate target (bpm)***	**RPE Borg scale**
**1**	75	55	(220-age × intensity %)^a^	
**2**	85	60		Light exercise
**3 and 4**	100	60		
**5 and 6**	110	65		
**7**	115	70		Moderate exercise
**8 and 9**	115	70		
**10 and 11**	130	75		Heavy breathing / sweating
**12 onwards**	150 (minimum)	75		

This exercise program is designed to encourage a gradual increase in physical activity over the course of 12 weeks. The starting point on the scale depends on the individual’s current fitness level.

From 12 weeks onwards, the aim is to achieve a minimum of 150 minutes per week of vigorous-intensity exercise.

RPE Borg Scale: Ratings of Perceived Exertion on a scale of 6 to 20; Heart rate in bpm (beats per minute*), ^a^for example, a 45 year-old man wishing to undertake exercise at 65% intensity would aim for a heart rate of (220 to 245) × 0.65 = 114 bpm [37].

All participants will be instructed to monitor their physical activity on a daily basis throughout the study using a wrist-worn heart rate monitor (Polar, Warwick, England) and physical activity log. The heart rate monitor will be worn whilst conducting exercise and will record the length of exercise and the heart rate during exercise. Participants will be requested to keep a daily log of activity and their blood glucose (BG). Participants will be asked to return the completed activity and BG logs to the research nurse at each visit. These will inform the subsequent discussion, and help monitor and encourage an increase in activity levels.

Use of the diary and heart rate monitor will be taught in the first meetings with the research nurse after randomization. Participants will negotiate appropriate targets with the nurse based initially on baseline values and subsequently on achievement. The setting of negotiated, realistic, achievable targets, and self-monitoring of progress towards these targets, is a key strategy for developing confidence to exercise (self-efficacy) and is a strategy adopted by many regular exercisers. All self-monitoring records will be reviewed by the research nurse. The activity log will be copied and returned to the participant, with written or verbal comments from the research nurse. The comments will highlight examples of positive changes the participant has made and help the participant address any barriers to physical activity encountered.

Participants who have not reached the activity goal of an extra 150 minutes per week of moderate to vigorous physical activity within four months of randomization will be offered further help to reach this target. An appointment will be made with a personal fitness instructor to examine alternative ways of helping them increase their activity. They will also be offered discounted membership at their local leisure center, where they will have access to gym and pool facilities and numerous supervised exercise classes (done through the exercise prescription). However, our previous experience indicates that such additional interventions are likely to be required in only a minority of cases.

#### Medical management

Management of T1DM, blood pressure, and lipid profile will be undertaken by the study team for the duration of the study. Any changes in treatment of these features will be made according to NICE guidelines [38] to keep the risk of performance bias to a minimum.

Glycemic control influences beta cell function, therefore our aim will be to achieve optimal glycemia in both arms of the study. To help with this, all patients will be managed either on insulin pump therapy or on a multiple dose insulin injection regime (fast acting or soluble insulin with each meal and background insulin at night). At each visit, the research nurse will review the patients blood glucose and make changes to insulin dosages if need be, and advice will be given about how to alter carbohydrate intake and insulin dosages to minimize hypoglycemic episodes with exercise and obtain ideal glucose control before, during and after exercise.

The overall aim will be to maintain the following targets: HbA1c concentration lower than 6.5%, blood pressure lower than 140/80 mmHg, total cholesterol concentration lower than 4·0 mmol/L, HDL cholesterol concentration higher than 1·0 mmol/L, LDL cholesterol concentration lower than 2·0 mmol/L, and concentration of triglycerides lower than 2·0 mmol/L.

### Assessment

Information will be collected on the number of patients diagnosed with T1DM, who have been approached and the reasons for not coming into the study, so that a full consort diagram can be generated (see Figure 1).

**Figure 1 F1:**
[figure not shown]
Consort diagram describing flow of patients through study.

Participants will be assessed at baseline, 6 and 12 months. A schedule and details of assessments that will be carried out are given in Tables 3 and 4.

The clinical examination, and assessment of HbA1c, lipids, and renal and thyroid function constitute part of good clinical care and will inform the clinical management of the patient.

Downloads from the heart rate monitor and review of the exercise diaries will confirm and quantify the exercise being undertaken by patients in the exercise arm. Data from the activity monitors will enable us to assess whether we have managed to increase activity in both arms of the study.

Changes across the study in the C peptide response to a mixed meal will enable us to determine the effect that exercise has on beta cell protection.

Measurement of inflammatory markers will inform on the antiinflammatory effect of exercise. Measurement of islet antibodies will allow confirmation and sub-classification of T1DM for the final analysis of the data.

### Safety

Written advice on carbohydrate and insulin dose adjustment around exercise will be prepared and distributed to both health care professionals and patients. The study team will keep in contact with subjects as they start and increase their exercise participation so that the risks of hypoglycemia and injury can be minimized. Any such events will be documented and reviewed at the study meetings.

### Planned sample size and analyses

A minimum of 30 patients per arm is considered sufficient to provide meaningful data to be obtained from this pilot study, but this will be reconsidered in the light of information gathered in phase 1. An initial recruitment rate of 30% is anticipated followed by a 90% adherence rate to the exercise schedule and a 15% drop-out rate. In order to complete the pilot study with a minimum of 30 patients, this means that 30/(0.85 × 0.9 × 0.3) = 130 patients will need to be approached initially.

With the varying sample sizes described above, estimates and 95% confidence intervals on recruitment rate, exercise adherence rate and drop-out rate will be:

Recruitment rate 30% (22% to 39%)

Adherence rate 90% (76% to 97%)

Drop-out rate 15% (5% to 30%)

Summary statistics (mean, standard deviation (SD), median, interquartile range (IQR), proportions) of demographic and primary outcome variables will be presented separately for intervention and control patients. Also, separately for intervention and control patients, change from baseline to 12 months in fitness related variables listed in Tables 3 and 4 will be estimated together with 95% confidence intervals. Trends over time in fitness related variables will be illustrated graphically. Variability in these changes will also be estimated in order to be able to estimate sample size requirements for a definitive trial. Comparison between intervention and control patients in change from baseline in fitness related variables will be made giving effect size estimates for the definitive trial. Association between fitness and demographic variables will be examined at a preliminary level using correlation analysis and chi-squared. A generalized linear model (GLM) will be used to get an initial impression of significance of differences between intervention and control groups in fitness related variables. Demographic variables and baseline fitness variable levels will be included as covariates. Further analysis will use non-linear mixed model analysis for outcome related fitness variables measures including the 19 sites as a random effect. Variation from site to site will then be used to further assist in the design of the definitive trial. The effect of demographic variables will also be investigated with mixed effect modeling.

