**Methods:**

Barriers to exercise will initially be assessed in a qualitative study of newly diagnosed patients. Then, sixty newly diagnosed adult type 1 diabetes patients will be randomized to either conventional treatment or exercise, stratified on beta cell function and fitness. The exercise group will be encouraged to increase their level of activity to a minimum of 150 minutes of moderate to vigorous intensity exercise per week, aiming for 240 minutes per week of exercise for 12 months. Beta cell function will be measured by meal-stimulated C peptide. Primary outcomes are recruitment, adherence to exercise, loss to follow-up, and exercise levels in the non-intervention arm (contamination). The secondary outcome of the study is rate of loss of beta cell function.

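### The number of patients to approach (130) is computed for 30 patients in the whole study, but the design calls for 30 per arm; at the plan's own rates it yields 39 randomised, not 60

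*Protocol article*

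**What the plan says.** All the figures are in the protocol article. Under Planned sample size and analyses, the target is given per arm: "A minimum of 30 patients per arm is considered sufficient to provide meaningful data to be obtained from this pilot study". The abstract's Methods paragraph gives the matching total: "sixty newly diagnosed adult type 1 diabetes patients will be randomized to either conventional treatment or exercise". The Randomization section confirms two equal arms: "Patients will be assigned, in a 1:1 ratio, to ‘usual care’ or ‘exercise intervention".

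The sample-size section then states its planning rates: "An initial recruitment rate of 30% is anticipated followed by a 90% adherence rate to the exercise schedule and a 15% drop-out rate". The next sentence turns these into a number to approach. It opens "In order to complete the pilot study with a minimum of 30 patients" and ends "this means that 30/(0.85 × 0.9 × 0.3) = 130 patients will need to be approached initially".

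Three anticipated estimates with 95% confidence intervals follow: recruitment ("Recruitment rate 30% (22% to 39"%), adherence 90% (76% to 97%) and drop-out 15% (5% to 30%).

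The abstract lists recruitment, adherence to exercise, loss to follow-up and contamination as the primary outcomes.

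**The concern.** Within one paragraph the target changes from 30 in each of two arms to 30 in the pilot as a whole, and the number to approach is built on the second figure. A reader planning from 130 would expect it to supply the 60-patient trial in the abstract, and at the stated rates it cannot.

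The chain has a second fault. It multiplies by 0.9 for adherence to the exercise schedule across all recruits. Usual-care patients have no such schedule. Exercise-arm patients who do not adhere are not lost either: their non-adherence is part of what the pilot sets out to measure.

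Two things are at stake: whether the planned pool of patients can fill the trial, and whether the advertised precision of three primary feasibility outcomes is right.

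**Working it through.** **Inputs** (Planned sample size and analyses, unless noted): recruitment 0.30; adherence 0.90; drop-out 0.15, so retention 0.85; 30 per arm; two arms at 1:1 (Randomization); 60 randomised (abstract).

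**Step 1. Reproduce the plan's figure.** 30 / (0.85 × 0.9 × 0.3) = 130.7. The printed 130 follows, apart from rounding down where rounding up gives 131. The arithmetic is sound; the numerator is the problem.

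**Step 2. Is 130 a per-arm figure?** Exact (Clopper-Pearson) 95% intervals show which denominators fit the printed ones.

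| Outcome | Printed interval | Count that fits | Exact interval |
|---|---|---|---|
| Recruitment | 22% to 39% | 39/130 | 22.3% to 38.7% |
| Adherence | 76% to 97% | 35/39 | 75.8% to 97.1% |
| Drop-out | 5% to 30% | 5/35 | 4.8% to 30.3% |

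These fit a single chain of 130 approached, 39 recruited, 35 adherent and 30 remaining. Had 130 been meant for each arm, about 260 would be approached in all, and 78/260 gives 24.5% to 36.0%, which is not what is printed. Patients are also approached and consented before they are allocated, so an approach number per arm has no natural meaning. The 130 is the whole-study figure.

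**Step 3. What 130 approached delivers at the plan's rates.**

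- Randomised: 130 × 0.30 = 39, or 19.5 per arm; 39/60 = 65%.
- Completing: 39 × 0.85 = 33.2, or 16 to 17 per arm; 33.2/60 = 55%.
- Completing and adherent, with adherence applied to everyone as in the printed formula: 33.15 × 0.9 = 29.8; 29.8/60 = 50%.

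**Step 4. What 30 per arm needs.**

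| Meaning of 30 per arm | Formula | Approached | Randomised |
|---|---|---|---|
| 60 randomised | 60/0.3 | 200 | 60 (60 × 0.85 = 51 completing) |
| 60 completing | 60/(0.85 × 0.3) = 235.3 | 236 | about 71 (60/0.85 = 70.6) |
| 60 completing, exercise arm also adherent | [30/(0.85 × 0.9) + 30/0.85]/0.3 = 248.4 | 249 | about 75 (39.2 + 35.3 = 74.5) |
| Printed formula with 60 | 60/(0.85 × 0.9 × 0.3) = 261.4 | 262 | about 78 |

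Every reading is well above 130. The third row implies slightly unequal arms (39.2 and 35.3). If strict 1:1 allocation must still yield 30 adherent completers in the exercise arm, that arm sets the number: 2 × 39.2 = 78.4 randomised, which is the fourth row.

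**Step 5. The intervals on appropriate denominators, taking 60 randomised** (exact method):

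- Recruitment 60/200: 24% to 37%, narrower than printed.
- Adherence 27/30, exercise arm only: 73% to 98%, wider than printed.
- Drop-out 9/60, all randomised: 7% to 27%, narrower than printed.

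**The case against.** The best defence is that 130 is a planning estimate and not a cap. The text speaks of a minimum and of an initial approach, says the size will be reconsidered after phase 1, and describes recruitment by calendar dates. Nothing stops sites approaching more than 130, and the target of 60 does not depend on that number. This is a pilot without a power calculation, and the 30% recruitment rate is itself something the study will estimate. All of this stands, and it limits the practical harm. It does not reconcile 30 per arm with 30 in total: the review after phase 1 concerns the minimum of 30 per arm, not the mismatch.

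Three stronger readings are tempting and should not be drawn:

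- A reader might infer that the plan delivers only half the trial. The half (29.8 of 60, or 130 against 262) appears only if the 0.9 factor is kept for both arms, which is itself a fault. Without it, the shortfall is 35% of those randomised or 45% of completers.
- A reader might infer that site targets or the recruitment period were derived from 130. The article prints no site targets and does not link its recruitment dates to that figure.
- A reader might infer that precision is overstated throughout. It is not: with 60 randomised, the recruitment and drop-out intervals would be narrower than printed. Only the adherence interval is too optimistic. No interval is given for contamination.

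It can also be argued that a pilot may want 30 exercisers who both complete and adhere. That is a legitimate aim. It would justify the 0.9 factor in the exercise arm, but not in usual care.

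**Conclusion.** The point holds as an internal contradiction with a definite size. The stated number to approach is for 30 patients in total, while the stated design is 30 per arm. At the plan's own rates 130 approached gives 39 of 60 randomised, a 35% shortfall, and about 33 of 60 completing, a 45% shortfall. The number consistent with the design is 200 if 30 per arm means randomised and about 236 if it means completing.

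The 0.9 factor is misapplied to usual care, and the printed adherence interval fits a count in which all 39 recruits are treated as exercisers.

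The conclusion assumes that the planning rates of 30%, 90% and 15% are right and apply equally in both arms. The recomputed intervals assume the exact method, which reproduces all three printed ones.

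**What to change.** In Planned sample size and analyses:

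1. State whether 30 per arm means randomised or completing, and make the abstract agree.
2. Restate the number to approach: 200 for 60 randomised (about 51 completing, 25 to 26 per arm), or about 236 for 60 completing (about 71 randomised).
3. Remove the 0.9 factor from usual care. If 30 completing and adherent exercisers are truly intended, say so and apply the factor to the exercise arm only (about 249, or 262 if the arms must stay equal).
4. Recompute the three intervals and print each denominator. For 60 randomised: recruitment 60/200, 24% to 37%; adherence 27/30 in the exercise arm, 73% to 98%; drop-out 9/60, 7% to 27%.

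The cost is a few corrected lines. The first option leaves the 60 randomised unchanged. The second raises the number randomised to about 71 and the abstract would have to change with it. Either option requires a larger pool of patients than the article now states, and the Discussion itself says that large numbers are hard to recruit in this population.

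### The effect size and SD for the definitive trial rest on change from baseline to 12 months in fitness variables; as written, they make no use of the 6-month values of patients who leave before 12 months

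*Protocol article*

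**What the plan says.** All of this stands in the protocol article. No statistical analysis plan is shown.

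- **Estimate by arm** (Planned sample size and analyses): "change from baseline to 12 months in fitness related variables listed in Tables 3 and 4 will be estimated together with 95% confidence intervals".
- **Variability**, next but one sentence: "Variability in these changes will also be estimated in order to be able to estimate sample size requirements for a definitive trial". The changes meant are those to 12 months.
- **Effect size**: "Comparison between intervention and control patients in change from baseline in fitness related variables will be made giving effect size estimates for the definitive trial". This sentence names no visit. The only change defined in the section is the one to 12 months.
- **Drop-out**: "An initial recruitment rate of 30% is anticipated followed by a 90% adherence rate to the exercise schedule and a 15% drop-out rate", with a stated interval for drop-out of 5% to 30%.
- **Visits** (Assessment, below Figure 1): "Participants will be assessed at baseline, 6 and 12 months". Table 4 places both the fitness test and the meal-stimulated C peptide test at weeks 24 and 48.
- **Other uses of repeated values** (Planned sample size and analyses): time trends are to be plotted. A GLM adjusts for baseline fitness and demographic variables. A later mixed model names site as its only random effect, and its stated use for design is between-site variation.
- **Beta cell function** (Research goals, item 4): the rate of loss in each arm is to refine the power calculation of the definitive trial. The analysis section names no estimator for it.

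**The concern.** The pilot exists to supply design figures for a definitive trial, so the estimator behind those figures matters more than any significance test here. A change score to 12 months exists only for patients seen at 12 months. Patients who attend at 6 months and then leave have given a post-randomisation value, yet the estimates named for design do not draw on it.

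Two things are at stake. The first is precision, in a trial with 30 patients per arm. The second is bias, if the patients who leave differ from those who stay in a way that their 6-month value would reveal. The protocol's Discussion lists the unsupervised nature of the intervention as a limitation, and only the exercise arm carries that burden, so drop-out that differs by arm is possible. The documents do not say that it will occur, or which patients would leave.

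**Working it through.** **1. The plan's own figures.** Patients to approach: 30/(0.85 × 0.9 × 0.3) = 30/0.2295 = 130.7, stated as 130. Exact 95% intervals: recruitment 39/130, 22.3% to 38.7%; adherence 35/39, 75.8% to 97.1%; drop-out 5/35, 4.8% to 30.3%. All agree with the stated intervals after rounding, so 15% is the plan's working drop-out rate.

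**2. How many lack a 12-month change.** With 30 randomised per arm, 30 × 0.85 = 25.5 per arm have one, or 51 of 60. About 9 do not.

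**3. Effect on the definitive trial, large-sample simulation.** The documents give no effect size, SD, alpha or power. Assumed: true effect 0.50 SD of change at both visits; correlation of 6- and 12-month change 0.5, 0.7 or 0.8; 15% leave after the 6-month visit; two-sided alpha 0.05; power 90%.

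- Patients per arm: n = 2 × (1.960 + 1.282)² × (SD/effect)² = 21.0 × (SD/effect)². For 0.50 and SD 1 this is 84.1, rounded up to 85.
- Real power at the n chosen: Φ(0.50 × √(n/2) − 1.960).

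Ranges run from correlation 0.5 to 0.8.

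| Drop-out after 6 months | Completers' effect | Completers' SD | n per arm chosen | Real power |
|---|---|---|---|---|
| Unrelated to response | 0.50 | 1.00 | 85 | 90% |
| Exercise arm only, moderate (odds ratio about 2.7 per SD of poorer 6-month change) | 0.56 to 0.61 | 0.99 | 66 to 56 | 82% to 75% |
| Exercise arm only, extreme (lowest 15% leave) | 0.64 to 0.72 | 0.98 to 0.94 | 50 to 37 | 71% to 58% |
| Lowest 15% leave each arm | 0.50 | 0.95 to 0.88 | 77 to 65 | 87% to 81% |

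An estimate that also uses the 6-month change gives 0.50 in every row, because here drop-out depends only on observed values.

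**4. Small-sample simulation.** Assumed: 30 per arm; correlations baseline–6 months 0.7, 6–12 months 0.8, baseline–12 months 0.6; true effect 0.50 SD; 15% leave after 6 months.

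- *Random drop-out*: root mean square error 0.25 for completers' change, 0.22 for the model using 6-month values. Much of that gain comes from the baseline covariate, which the plan's GLM already has.
- *Exercise arm only, poor responders leave*: completers' change averages about 0.59 to 0.61, error 0.27. The 6-month model averages 0.49 to 0.50, error 0.22. A completers' model adjusted for baseline lies between: mean about 0.57, error 0.24.
- *One absolute response rule in both arms*: more controls leave, because fewer of them improve. Completers' change falls to about 0.44 or 0.45 (0.43 to 0.48 over moderate settings).
- *Equal proportions leave each arm on relative response*: completers' change is 0.50.

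The direction of the bias therefore depends on the mechanism.

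**The case against.** The case against has several parts.

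*Estimating a change to 12 months does not prescribe raw subtraction among completers.* True: a repeated-measures model can estimate the same quantity. A reader might infer that the 6-month data are thrown away. The text does not say so. They are plotted, and they could enter the mixed model, whose visit structure is not given. What stands is narrower: nothing links them to the effect size or SD passed on, and the mixed model's stated design use is a different one.

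*Handling of missing values belongs in an analysis plan that is not shown.* Also true, and its absence from an article is no fault. The point concerns the estimator that the article names as the source of the design figures.

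*The quoted sentences concern fitness, not C peptide.* This stands. A reader might conclude that the definitive trial would be sized on a completers' effect in beta cell function. The article fixes no such estimator, and a rate of loss can use the 6-month value.

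*Sampling error outweighs the bias.* In the adverse case, the sampling SD of completers' change was 0.25, against a bias of about 0.09 to 0.11. This limits the practical harm. It does not favour completers' change, which had the larger error in every scenario tried.

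**Conclusion.** The concern holds in limited form. For fitness variables, the stated inputs to the definitive trial depend on a 12-month value that about 15% are expected to lack, and the scheduled 6-month values do not contribute to them as written.

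The consequence is conditional. Random drop-out costs some precision and causes no bias. Selective loss in the exercise arm alone inflates the effect to about 0.56 to 0.61 against 0.50 SD under moderate selection; a trial sized on that for 90% power would have 82% to 75%. Two further inferences are tempting and unsupported. One is that leavers are likely to be non-improvers: no passage says this, and adherence and drop-out are listed as separate rates. The other is that loss of poor responders in both arms must make the effect too small: that needs one absolute threshold acting in both arms, and with equal proportions leaving on relative response only the SD shrinks.

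The effect sizes, correlations and mechanisms are all assumptions. Patients who leave before 6 months gain nothing from the alternative. The case for the change is that it is nearly free, not that the plan's estimate is known to be biased.

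**What to change.** State that the 12-month between-arm contrast and its SD for the definitive trial come from one participant-level linear repeated-measures model:

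- outcomes: the 6- and 12-month values, from all randomised patients with at least one of them;
- terms: baseline value as covariate, arm, visit and arm by visit;
- correlation of the two visits within a patient;
- reported: the 12-month contrast with its 95% confidence interval, and the 12-month SD.

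Keep completers' change from baseline to 12 months as a sensitivity analysis. Use the same model for C peptide, because Research goals item 4 needs its effect size and the analysis section states no estimator for it. The mixed model with site can stay for its own purpose.

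Cost: a few lines of analysis-plan wording and one model, with no new visits or data. Downside: the model assumes that drop-out is explained by the observed values. If patients leave for reasons that their baseline and 6-month values do not show, some bias remains.
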